#### 2.9.2. Statistical Methods

##### Primary and Secondary Analyses (MBS Group)

The primary analysis will be performed using linear mixed models, adjusted for confounders. Mean glycemia refers to the mean interstitial glucose level measured via CGM throughout pregnancy. Glycaemic variability reflects fluctuations in blood glucose levels and is quantified using variables such as SD, CV, and MAGE derived from CGM. Repeated measurements will be used for the primary outcome analysis, with mean glycemia and glycaemic variability treated as continuous outcome variables, and birth weight as the explanatory variable. To account for clustering due to repeated measures, linear mixed models will be used with a random intercept for the subject. Confounders such as smoking, hypertension, nutrient deficiencies, insufficient gestational weight gain, and time from surgery will be added to the model as covariates to determine the independent association between birth weight and glycaemic parameters. Variables will be considered confounders if they are associated with both birth weight and glycaemic parameters. Linear slopes with 95% confidence intervals will describe the association between glycaemic parameters and birth weight. No specific action is taken to deal with missing CGM results given the fact that the analysis model is likelihood-based and known to provide unbiased results under the fairly general assumption of missingness at random [42]. Statistical analysis will be performed by SAS version 9.4; all tests will be two-sided with significance set at *p* < 0.05.

Secondary outcomes, including time spent <54 mg/dL and hyperglycaemic thresholds (>120 mg/dL and >140 mg/dL), will be analysed analogously.

Third, associations between glycaemic patterns and binary neonatal outcomes, including SGA and birth defects, will be assessed similarly using linear models for repeated measurements. Mean differences with 95% confidence intervals will be estimated between cases with and without the specified adverse outcome.

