
## 1. Background

Obesity is associated with increased risks for miscarriages, gestational diabetes mellitus (GDM), preeclampsia, and caesarean delivery [1]. Metabolic and bariatric surgery (MBS) is the most effective treatment for obesity and its related comorbidities [2]. Of all patients who undergo MBS, up to 80% are women of childbearing age [3]. As such, pregnancies in women with a history of MBS are becoming increasingly prevalent. Surgically induced metabolic changes benefit mother and child but can also lead to adverse pregnancy outcomes. Several nationwide register-based cohort studies and systematic reviews have shown that MBS is associated with lower risks for macrosomia, GDM, and hypertensive disorders, but with increased rates of small-for-gestational-age (SGA) infants, preterm delivery, and perinatal mortality [4,5,6,7,8]. Children born SGA are at an increased risk of developing type 2 diabetes and cardiovascular diseases in the long-term [9]. The fact that the increased risks of SGA and preterm deliveries remain when matching for pre-pregnancy weight suggests that MBS as such is associated with adverse obstetric outcomes, and not only through weight reduction [7]. A continuous decline in foetal growth throughout pregnancy has been demonstrated after Roux-en-Y gastric bypass (RYGB), starting at the beginning of the second trimester [10]. In addition, the foetal abdominal subcutaneous tissue thickness (FASTT) was markedly decreased in foetuses of mothers with a history of MBS [11].

The underlying mechanisms of foetal growth restriction in this population remain unclear but are likely multifactorial. Potential contributors include nutrient deficiencies, placental dysfunction, altered glucose metabolism, and potentially changes in other metabolic pathways. A prospective cohort study including 54 women with previous MBS confirmed reduced foetal growth in pregnancies following surgery and evaluated fetoplacental Dopplers as a proxy for placental function [12]. However, no alterations in fetoplacental circulation or correlations with foetal size were observed [12].

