### 2.3. Objectives

This trial is designed to show with 80% power a linear association between mean glycemia or glycaemic variability and birth weight in a pregnancy after MBS. The hypothesis is that an altered metabolic profile including an altered glucose metabolism (with increased time spent in hypoglycaemia and greater glycaemic variability) and altered metabolomics during pregnancy after MBS contribute to the increased risk of adverse pregnancy outcomes such as SGA and preterm delivery. In addition, we hypothesise that concentrations of branched-chain and aromatic amino acids, and unsaturated lipids in the third trimester of pregnancy, are lower in pregnant women with MBS, and that this is also associated with a lower birth weight.

This study aims to evaluate whether biomarkers derived from CGM and metabolomic profiling in pregnancies following MBS are associated with foetal growth and newborn body composition.

The following specific aims will be addressed.

Primary aim: To determine whether altered glucose metabolism (including lower mean blood glucose levels, hypoglycaemia, and glycaemic variability) measured by CGM in pregnancy after MBS is related to delayed foetal growth.

Exploratory objectives:To compare glucose metabolisms between pregnant women after MBS and age- and BMI-matched pregnant women without MBS.To determine whether metabolic alterations are associated with delayed foetal growth in pregnant women after MBS compared to pregnant women without MBS, and, in particular, which metabolites are related to adverse outcomes in pregnancy.To determine whether there are differences in glucose metabolism and other metabolites (by using metabolomics) between RYBG and SG.To determine the impact of MBS on the body composition of newborns.To determine the accuracy of CGM compared to the self-monitoring of capillary blood glucose (SMBG) to screen for GDM in pregnant women with MBS.

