#### 2.3.1. Primary Outcome

In the surgical group, we will assess mean glycaemia as a continuous outcome variable, glycaemic variability (standard deviation) as a continuous outcome variable, and birth weight as a continuous explanatory variable. Linear mixed models will be used for the primary outcome analysis. The outcome variables will be measured at four time points for each subject. Confounders will be added to the model as covariates.

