### 2.9. Statistics

This study examines the association between glycaemic patterns during pregnancy after MBS and birth weight. The primary aim is to assess whether glycaemic dysregulation (e.g., hypoglycaemia, glycaemic variability) contributes to foetal growth restriction in this population.

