#### 2.9.1. Sample Size and Power Calculation

The sample size (n = 95) was calculated based on the best available data on CGM in pregnancy with MBS [40,41]. The study provides 80% power to detect a moderate association (effect size = 0.3) between glycaemia measures (mean and variability) and birth weight at a significance level of *p* < 0.05. Repeated CGM measurements (four one-week periods per participant) were accounted for using a cluster size of four and assuming an interclass correlation (ICC) of 0.5. A drop-out rate of 30% was assumed, in the sense that 30% of all measurements would be missing. The sample size was decided considering adjustment for four variables in the analysis. A Bonferroni correction will be applied to control for multiple comparisons, resulting in a 2.5% test-wise significance level.

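### The primary model estimates glucose per gram of birth weight, which is not the quantity needed for the stated aim of whether glycaemia contributes to growth restriction

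*Protocol article*

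**What the plan says.** Section 2.3.1 (Primary Outcome) makes mean glycaemia and its standard deviation the outcomes, measured at four time points, with "birth weight as a continuous explanatory variable". Section 2.9.2 (Primary and Secondary Analyses) repeats this, "with mean glycemia and glycaemic variability treated as continuous outcome variables, and birth weight as the explanatory variable", in a mixed model with a random intercept per woman and confounders as covariates. The effect measure is fixed there too: "Linear slopes with 95% confidence intervals will describe the association between glycaemic parameters and birth weight". Section 2.3.2 uses the same direction for adverse pregnancy outcomes.

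The purpose is worded in two ways. Section 2.3 is neutral about direction: "This trial is designed to show with 80% power a linear association between mean glycemia or glycaemic variability and birth weight". Section 2.9 is directional: "The primary aim is to assess whether glycaemic dysregulation (e.g., hypoglycaemia, glycaemic variability) contributes to foetal growth restriction in this population". The hypothesis in section 2.3 and the closing paragraph of the Discussion are directional as well; both treat glucose metabolism as something that influences outcomes.

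On size, section 2.9.1 states: "The study provides 80% power to detect a moderate association (effect size = 0.3) between glycaemia measures" and birth weight. It assumes four measurements per woman, an ICC of 0.5, 30% of measurements missing, adjustment for four variables and a 2.5% test-wise level.

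**The concern.** With glucose as response and birth weight as predictor, the slope is the difference in glucose, in mg/dL, between women whose infants differ by one gram at birth. The aim in section 2.9 needs the other conditional expectation: how much birth weight differs between women who differ by one unit of mean glucose or of SD. The article plans no model for that in the surgical group and no conversion to it.

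The published effect would therefore not be on the scale needed to judge whether an association is large enough to matter for growth. The Discussion expects the data to serve future meta-analyses, where the scale matters again. The reciprocal of the slope looks like an easy way across and is wrong by a large factor.

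**Working it through.** **1. Reproduce the planned size.** Inputs are from section 2.9.1, with 0.3 read as a correlation (the article does not name the scale).

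- Fisher z with four covariates at two-sided 0.025: ((2.241 + 0.842)/atanh(0.3))² + 3 + 4 = 106.2.
- Design effect 1 + (4 − 1) × 0.5 = 2.5.
- 106.2 × 2.5 / 4 / 0.7 = 94.8, so 95.

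This matches the stated n. Using alpha 0.05 gives 80, and omitting the covariates gives 92. A correlation is symmetric, so the size does not depend on the direction of the regression.

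**2. Check the test in both directions.**

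- One simulated data set of 95 women with four covariates, ordinary regression each way: p = 0.00213 in both directions.
- 400 simulated trials (95 women, four visits, ICC 0.5, measurement-level correlation 0.3, 30% missing, no confounders): power at alpha 0.025 was 0.905 for the planned mixed model and 0.905 for birth weight regressed on each woman's mean glucose. The two gave the same verdict in 98.5% of trials.

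**3. Compare the estimates.** The article gives no standard deviations. Assume 10 mg/dL for a single-period glucose mean and 500 g for birth weight. Their covariance is 0.3 × 10 × 500 = 1,500, and it is the same whether glucose is one measurement, a woman's observed mean or her underlying mean. With 30% missing, 4 × 0.7 = 2.8 measurements remain per woman.

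- Planned slope: 1,500/500² = 0.006 mg/dL per g (0.6 mg/dL per 100 g). Its reciprocal is 167 g per mg/dL.

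| Glucose exposure | Variance | Birth-weight slope (g per mg/dL) | Reciprocal too large by |
|---|---|---|---|
| Single measurement | 100 | 1,500/100 = 15 | 1/0.09 = 11.1 |
| Observed mean of 2.8 | 100 × (1 + 1.8 × 0.5)/2.8 = 67.9 | 1,500/67.9 = 22.1 | 0.679/0.09 = 7.5 |
| Underlying mean | 100 × 0.5 = 50 | 1,500/50 = 30 | 0.5/0.09 = 5.6 |

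The simulation agrees: mean planned slope 0.0059 mg/dL per g, reciprocal 170, against 21 for the observed mean (8-fold) and 30 for the underlying mean (about 6-fold).

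The factors in the last column do not depend on the assumed SDs; the slopes do. At measurement level, glucose SDs of 8 to 15 mg/dL and birth-weight SDs of 450 to 550 g give planned slopes of 0.44 to 1.0 mg/dL per 100 g, birth-weight slopes of 9 to 21 g per mg/dL, and reciprocals of 100 to 229.

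**4. Can the planned slope be converted properly?** Yes, under a linear joint-normal model with the same covariates.

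- In the ordinary regression check, partial r² = t²/(t² + df) = 0.101, and 0.101/0.364 = 0.278, which is the forward slope. The simple reciprocal, 1/0.364, is 2.75.
- In the mixed model, the slope is multiplied by the birth-weight variance and divided by the between-woman glucose variance: 0.006 × 250,000/50 = 30. The simulation returned 29.4.

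The article plans neither step, and the answer depends on which glucose exposure is meant.

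**The case against.** The best defence is that the article promises an association and tests one. The abstract, section 2.3 and the opening of section 2.9 all use that word, and steps 1 and 2 show that the test and the size hold up. The direction is used consistently and has a real advantage: the repeated, partly missing CGM measurements sit on the response side, where the likelihood handles them under missingness at random. It also resembles the earlier comparison, described in the Background, of glycaemia in pregnancies that did and did not end with an SGA infant. All of this stands. It does not supply the quantity that the directional sentence in section 2.9 asks for.

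A reader might go further in four ways that the document does not support.

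- **That the slope cannot be converted at all.** Step 4 shows that it can; only the simple reciprocal fails.
- **That the plan contains an 11-fold error.** Nothing in the article inverts the slope. The factor describes a misreading that the plan leaves open, and 11 is the single-measurement figure.
- **That visit and birth-weight-by-visit terms are wrongly left out.** The Background places the decline in foetal growth after gastric bypass as "starting at the beginning of the second trimester". That concerns growth and does not show that the glucose slope varies by visit. The article does not exclude a visit term, a condensed article need not list every fixed effect, and it poses no visit-specific question. Section 2.8.9 also reports CGM metrics as relatively stable across trimesters, though in uncomplicated pregnancies.
- **That modelling mean glucose and SD separately is a mistake.** Section 2.3 joins them with an or, and section 2.9.1 splits alpha for two tests. Mutual adjustment is useful but is not a stated primary aim.

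**Conclusion.** The point holds as a mismatch between the reported estimate and the directional aim. It does not make the primary test invalid or the study too small. The planned slope, in mg/dL per gram, does not give the birth-weight difference per unit of glycaemia, and nothing else planned in the surgical group does.

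A simple reciprocal would overstate that difference about 11-fold at measurement level and about 6 to 8-fold for a woman's own glucose level. These factors rest on reading 0.3 as a measurement-level correlation, which reproduces n = 95, and on the plan's ICC of 0.5 and 30% missing measurements. The slopes in grams also rest on assumed SDs. The change is worth making before analysis.

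**What to change.** Keep the planned mixed model as the hypothesis test, with its alpha split and sample size unchanged. Add one reported estimation model per metric, with birth weight as outcome, each woman's CGM mean glucose or SD as exposure, and the same confounders. Report grams per unit with a 95% confidence interval. Obtain the exposure from a joint model, or from subject-level values of the mixed model, so that missing sessions are handled. Entering mean and SD together is an optional extra that would show whether variability relates to birth weight beyond mean glucose.

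If no such model is wanted, reword the aim in section 2.9 and the closing paragraph of the Discussion so that they claim association only.

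The cost is one more model per metric on data already collected. Subject-level CGM values carry measurement error, which a joint model addresses. The added model should be labelled as estimation, because its own power depends on the level at which 0.3 applies. At n = 95, alpha 0.025 and four covariates, power is 0.91 to 0.93 if 0.3 is the measurement-level correlation (2.8 to 4 measurements per woman) and 0.75 if it is the subject-level one.

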#### 2.8.1. Screening Visit

The study will be introduced at first prenatal visit by a physician or midwife. Interested women will receive a summary information sheet and the informed consent form. Women will have at least 24 h to consider their decision, after which the local research team will follow up on their choice. Informed consent can only be signed if all inclusion and exclusion criteria have been met. Pregnant women can only participate in the control group if a one-on-one match is identified with a participant in the surgical group. The coordinating investigator will maintain a password-protected log containing BMI and age data for all study participants to ensure accurate matching.

#### 2.8.2. Visit 1 to 4

Women will be recruited at first prenatal visit (before 12 weeks). To evaluate glucose homeostasis, a masked CGM will be used for 10 days at the following time points: between 6 and 12 weeks of pregnancy, at 18–22 weeks of pregnancy, at 24–28 weeks of pregnancy (when screening for GDM, and at 30–34 weeks of pregnancy. At each visit with CGM, clinical examination will be performed, questionnaires will be completed, and micronutrients will be measured (as described below). As standard of care in the surgical group, follow-up by a dietician during pregnancy will be provided according to need or at the indication of the treating physician. A purpose designed multivitamin preparation (BariNutrics^®^ Prenatal) will be started at periconception. In each trimester, micronutrients will be checked by blood analyses of vitamin A, vitamin D, B12, folate, prothrombin time iron, transferrin saturation, and ferritin, for the surgical group. Deficiencies detected at any time point will be addressed by the prescription of targeted extra supplementation by the treating physician.

A standardised protocol will be used to screen for diabetes in early pregnancy and GDM later in pregnancy for both groups.

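### The primary mixed model names no visit term, so its claim to be unbiased under missingness at random fails if glucose trends over gestation and loss of late sessions is related to birth weight

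*Protocol article*

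**What the plan says.** The primary model is described in sections 2.3.1 and 2.9.2 of the protocol article.

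- **Outcome and predictor:** "with mean glycemia and glycaemic variability treated as continuous outcome variables, and birth weight as the explanatory variable".
- **Repeated measures:** "The outcome variables will be measured at four time points for each subject". Section 2.8.2 places the sessions "between 6 and 12 weeks of pregnancy, at 18–22 weeks of pregnancy, at 24–28 weeks of pregnancy", with a fourth at 30–34 weeks.
- **Clustering:** "To account for clustering due to repeated measures, linear mixed models will be used with a random intercept for the subject".
- **Covariates:** "Confounders such as smoking, hypertension, nutrient deficiencies, insufficient gestational weight gain, and time from surgery will be added to the model as covariates". The list is open, but all five examples describe the woman or her pregnancy, not the session.
- **Covariate rule:** "Variables will be considered confounders if they are associated with both birth weight and glycaemic parameters".
- **Missing sessions:** "No specific action is taken to deal with missing CGM results given the fact that the analysis model is likelihood-based", a model described as "known to provide unbiased results under the fairly general assumption of missingness at random".

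Neither section names visit, gestational age or time. Section 2.9.1 expects 30% of all measurements to be missing.

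**The concern.** The validity of a likelihood analysis under missingness at random depends on a correctly specified mean. Here the mean at each session is birth weight plus covariates, the same at 8 weeks as at 32 weeks. Suppose glucose changes across gestation and women with lighter babies lose late sessions more often. Missingness then depends on birth weight, which is observed and in the model, so the data are missing at random. Yet the slope is still biased: women with lighter babies are represented by earlier sessions and women with heavier babies by later ones, and the model can only attribute the difference to birth weight.

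The covariate rule does not repair this. Visit is set by design and is the same for every woman, so with complete data it has no association with birth weight and does not qualify as a confounder.

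Both conditions are plausible. Section 2.3 expects more preterm delivery and SGA in this population, and section 2.7 allows discontinuation after adverse events. The direction of the bias follows the trend. If late sessions are lost mainly at low birth weight, a rising trend pushes the slope upward. That would exaggerate the hypothesised positive slope for mean glucose and mask the hypothesised negative slope for variability. A falling trend does the reverse.

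**Working it through.** **1. The plan's own figure.** Inputs from sections 2.9.1 and 2.9.2: effect size 0.3 (read as a correlation), 80% power, two-sided test-wise level 0.025, four covariates, four sessions, ICC 0.5, 30% of measurements missing.

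- Independent n = ((2.241 + 0.842) / atanh 0.3)² + 3 + 4 = (3.083 / 0.3095)² + 7 ≈ 106.2.
- Design effect = 1 + (4 − 1) × 0.5 = 2.5. Sessions per woman = 4 × 0.7 = 2.8.
- N = 106.2 × 2.5 / 2.8 ≈ 94.8, rounded up to 95.

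The stated n reproduces. The point concerns bias, not sample size.

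**2. How the bias arises.** Take assumed visit means of 0, 0.2, 0.6 and 1.0 SD (a 1 SD rise).

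- All four sessions: (0 + 0.2 + 0.6 + 1.0) / 4 = 0.45.
- Last session lost: (0 + 0.2 + 0.6) / 3 = 0.27.
- Last two lost: (0 + 0.2) / 2 = 0.10.

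Two women with identical glucose profiles thus differ by 0.18 or 0.35 SD in their observed averages. If the loss is unrelated to birth weight, this is noise. If it is related, it enters the slope.

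**3. Size by simulation.** Common inputs: 95 women, ICC 0.5, about 30% of sessions missing, total glucose SD 1, REML random-intercept fits with and without a four-level visit factor. Slopes are in SD of glucose per SD of birth weight. The trend size and the link between missingness and birth weight are assumptions.

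| Missingness | Trend, visit 1 to 4 | Bias without visit | Bias with visit |
|---|---|---|---|
| None, or unrelated to birth weight | up to 1 SD | about 0 | about 0 |
| Session by session, late visits linked (log-odds 0.5–1.0 per SD) | 0.5–1 SD | 0.02–0.07 | about 0 |
| Permanent dropout, log-odds 0.5 | 0.25 / 0.5 / 1 SD | 0.018 / 0.031 / 0.055 | at most about 0.004 |
| Permanent dropout, log-odds 1.0 | 0.25 / 0.5 / 1 SD | 0.024 / 0.055 / 0.101 | at most about 0.004 |
| Only the lowest 5–10% of birth weights lose visit 4 | up to 1 SD | 0.004–0.024 | at most about 0.004 |

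Against the 0.3 target, 0.02 to 0.07 is 7% to 23% (0.02/0.3 and 0.07/0.3). The most severe permanent-dropout case is 34% (0.101/0.3).

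**4. Error rates at the nominal 2.5% level.**

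- Session-by-session loss: type I error reaches 5.6%. Power falls from 87% to about 60% in the worst case, when the trend opposes the effect.
- Permanent dropout, log-odds 1.0, 1 SD trend: type I error is 13.7% without visit and 2.5% with it.
- Preterm-only loss: 2.5% to 3.4%, close to nominal.

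**The case against.** **The document is a condensed article.** The covariate list is open and the full protocol and SAP are not shown. Coding of visit is often settled there. This stands: one cannot conclude that the analysts will omit visit. What remains is that the published text pairs a covariate rule that visit would not meet with an unqualified claim of unbiasedness.

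**The rule defines confounders, not design terms.** This is also fair. Moreover, when late sessions are lost selectively, visit becomes associated with birth weight among the observed sessions, so the rule read literally might admit it. In one check, a simple test flagged that association in about half of runs at log-odds 1.0 but in only about 2% at 0.5. The primary model should not depend on such a screen.

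**The trend may be small.** Section 2.8.9 reports that CGM metrics change little across trimesters. It is the document's only statement on the matter, but it concerns uncomplicated pregnancies, not women after MBS, and gives no figure.

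**Loss may be only weakly related to birth weight.** The last window closes at 34 weeks, so later preterm births lose nothing. Noncompliance and long-term corticosteroids, also listed in section 2.7, have no stated link to birth weight. This stands, and is why the preterm-only scenario gives so little bias.

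**Stronger readings.** A reader might infer that any gestational trend leaks into the slope whenever late sessions are missing. It does not: with loss unrelated to birth weight the bias was about zero for trends up to 1 SD. A reader might also want a visit-by-group term in the MBS–control comparison. That analysis is labelled exploratory, no error is shown in it, and the term would be a preference.

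**Conclusion.** The point holds in conditional form. As described, the primary model has no term for gestational timing, and the justification for taking no action on missing sessions is stated too broadly for it. Bias requires both a gestational trend and loss of late sessions related to birth weight. Both are plausible in this population; neither is quantified in the document.

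Under assumed trends of 0.5 to 1 SD and log-odds of 0.5 to 1.0 per SD of birth weight, the bias is about 0.02 to 0.07 SD, with larger values (to about 0.10) only if the loss is permanent dropout strongly tied to birth weight. It is near zero if only a few early preterm births lose the last session. Including visit removes it in every scenario examined. The correction should be made because it protects the primary analysis at almost no cost, not because serious bias has been shown to be likely.

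**What to change.** In section 2.9.2, state that study visit (four-level factor), or gestational age at sensor start, is always a fixed effect in the MBS-group repeated-measures models, irrespective of the confounder rule. Secondary outcomes analysed in the same way should carry the same term. Reword the missing-data sentence so that validity under missingness at random is claimed for that model. If the SAP already includes visit, only the published wording needs correcting.

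The cost is three degrees of freedom out of about 95 × 4 × 0.7 = 266 expected sessions. No new data are needed, and n = 95 need not change because visit varies within women. With no trend and a true slope of 0.3, simulated power was 91.9% both with and without visit when 30% of sessions were lost at random. Under the strongest dropout link it was 89.4% with visit and 90.0% without.

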## 3. Discussion

This large longitudinal cohort study aims to investigate whether pregnancy following MBS is associated with altered maternal glucose profiles, as assessed by CGM, and whether these alterations are linked to differences in foetal growth and newborn body composition. Outside of pregnancy, altered glucose patterns after MBS have been well-documented [18]. Emerging data suggests that pregnancies following RYGB are marked by significant glycaemic variability, including frequent episodes of both hyper- and hypoglycaemia. However, most studies to date are small and cross-sectional. Bonis et al. first reported wide glucose fluctuations and substantial hyperglycaemia in mid-pregnancy CGM profiles of post-RYGB women, resembling patterns seen in the non-pregnant post-RYGB population [40]. Leutner et al. similarly found increased glycaemic variability, including more frequent day and nighttime hypoglycaemic events compared to pregnant controls [41]. In a larger retrospective study, Gohier et al. found that 73% of women had abnormal time in range (TIR), and found associations between hypoglycaemia and prematurity, while SGA was paradoxically linked to lower hypoglycaemia exposure [44]. Additionally, an observational cross-sectional study comparing pregnancies after RYGB and SG found that while mean glucose levels were similar, women post-RYGB experienced greater glycaemic variability and spent less time in the target glucose range, indicating more pronounced glucose fluctuations following RYGB [45]. The only longitudinal data come from Stentebjerg et al., who performed CGM across all trimesters, demonstrating that, compared to BMI- and parity-matched controls, these pregnant women spent more time in both hyperglycaemia and hypoglycaemia. They also observed a modest association between increased time spent in hypoglycaemia and SGA outcomes [21]. Overall, while evidence points to a distinct glycaemic profile in post-RYGB pregnancies, none of these earlier studies were sufficiently powered to show the implications on foetal growth [21].

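### The primary model's covariates are governed by two conflicting sentences, one of them an association rule that can drop real confounders; the set should be fixed in advance and should name surgery type

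*Protocol article*

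**What the plan says.** Section 2.9.2 (Primary and Secondary Analyses) specifies a linear mixed model with a random intercept per woman. Mean glycaemia and glycaemic variability are the outcomes and birth weight is the explanatory variable. On covariates it says: "Confounders such as smoking, hypertension, nutrient deficiencies, insufficient gestational weight gain, and time from surgery will be added to the model as covariates". The next sentence reads: "Variables will be considered confounders if they are associated with both birth weight and glycaemic parameters". No data source, threshold or timing is given for that judgement.

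Other parts of the article bear on it:

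- Section 2.9.1: "The sample size was decided considering adjustment for four variables in the analysis". Section 2.9.2 names five variables as examples, and the Abstract names three.
- Section 2.9.2 (Exploratory Comparative Analyses) keeps covariates in the control comparison if they are found to differ between the groups.
- Section 2.1 expects 30 to 50% of participants to have had sleeve gastrectomy. The Discussion cites a study in which "women post-RYGB experienced greater glycaemic variability and spent less time in the target glucose range"; the same sentence says that mean glucose was similar. Surgery type appears in neither covariate list.

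**The concern.** The two covariate sentences pull apart. Under the first, the named variables go in. Under the second, a variable goes in only if it turns out to be associated with both birth weight and glycaemia. A reader cannot tell which model is primary.

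Taken as a screen in the study data, the second sentence has two weaknesses. First, with 95 women a moderate confounder often fails to show an association with both variables. It is then dropped, its bias stays in the slope, and the final p-value ignores the selection. Second, the screen cannot separate a confounder from a variable on the pathway, because a mediator is also associated with both. Insufficient gestational weight gain accrues during pregnancy, and micronutrients are measured each trimester (section 2.8.4), so both run alongside the glucose monitoring. Whether the primary slope is a total or a direct association would then depend on what the screen happened to keep.

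What is at stake is the meaning and the error rate of the one confirmatory result.

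**Working it through.** **1. Reproduce the sample size.** Inputs, all from section 2.9.1 unless noted:

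- "The study provides 80% power to detect a moderate association (effect size = 0.3) between glycaemia measures (mean and variability) and birth weight". The scale of 0.3 is not named; I read it as a correlation.
- "A Bonferroni correction will be applied to control for multiple comparisons, resulting in a 2.5% test-wise significance level", two-sided (section 2.9.2).
- "using a cluster size of four and assuming an interclass correlation (ICC) of 0.5".
- 30% of measurements missing; four covariates.

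Steps:

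- n0 = ((z(0.9875) + z(0.80)) / atanh(0.3))² + 3 = ((2.241 + 0.842) / 0.3095)² + 3 = 102.2
- Add four covariates: 106.2
- Design effect = 1 + (4 − 1) × 0.5 = 2.5
- N = 106.2 × 2.5 / 4 / 0.70 = 94.8, so 95

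The stated 95 is reproduced, with power 80.1%. A two-sided 5% level gives 80 instead, so 2.5% is used below.

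**2. Cost of more fixed covariates, same formula.**

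| Covariates | N needed | Power at 95 |
|---|---|---|
| 4 | 94.8 | 80.1% |
| 5 (those named) | 95.7 | 79.6% |
| 6 (those named plus surgery type) | 96.6 | 79.2% |

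**3. Effect of the rule if used as a screen.** The protocol gives no confounder strengths and no threshold, so these are assumptions: true slope zero, independent confounders, 95 women, and a covariate kept if p<0.05 with both variables. Simulated false-positive rates at a nominal 2.5%:

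| Assumed confounding | Rule | Fixed set |
|---|---|---|
| Four, each 0.2, same direction | about 7% | 2-3% |
| Five, each 0.2, same direction | 10-11% | 2-3% |
| Each 0.1, same direction | 3.0-3.4% | 2-3% |
| Each 0.2, signs balanced (2+/2− or 3+/2−) | 2.1-3.0% | 2-3% |
| Each 0.2, same direction, screen at p<0.2 | 3.2-4.0% | 2-3% |

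In the 0.2 case with four confounders, about one of the four is retained on average.

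A second simulation followed the actual design: four periods, 30% missing, ICC 0.5, and five same-direction candidates. It gave 3.0% with no confounding, 3.2% at 0.1, 9.8% at 0.2, 14.8% at 0.3 and 22.6% at 0.4. Coverage of the 95% interval was 94%, 94%, 85%, 78% and 72%. Fixed adjustment stayed at 1.9 to 3.1%, with coverage of 94 to 96%.

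**4. Adjusting for a pathway variable.** Effective N = 95 × 4 × 0.70 / 2.5 = 106.4. The partial correlation is (0.3 − r_gm × r_mb) / √((1 − r_gm²)(1 − r_mb²)), where r_gm and r_mb are the variable's assumed correlations with glucose and with birth weight. Power is Φ(√103.4 × atanh(r) − 2.241).

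- No adjustment: r = 0.30, power 82%
- r_gm 0.2, r_mb 0.3: 0.24 / √(0.96 × 0.91) = 0.26, power 67%
- r_gm 0.3, r_mb 0.4: 0.18 / √(0.91 × 0.84) = 0.21, power 45%

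This counts as a loss only if the total association is the target.

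**5. Surgery type left out.** I assumed 40% sleeve gastrectomy, a true slope of zero, and standardised differences by procedure. The false-positive rate is 2.7% (0.2 on birth weight, 0.5 on glycaemia), 3.0% (0.3, 0.5), 3.7% (0.5, 0.5) and 7.6% (0.5, 0.8). If surgery type is a candidate under the rule, it is 2.2 to 3.0%.

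**The case against.** The strongest reply is that the screen simulated above is not written in the protocol. The article names no data source and no p-value, and its preceding sentence says outright that the five variables go in. If that sentence governs, the selection results do not apply. The article is also condensed, and the final list may sit in an analysis plan that is not shown. The first part stands as a limit on the numbers. It does not remove the point: the rule is stated, it contradicts its neighbour, and the control comparison uses the same data-driven approach.

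A reader might go further than the document allows in five ways:

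- **That the slope is biased and the test level is missed.** Inflation needs several moderate confounders pushing the same way and a strict screen. With weak or balanced confounding it largely disappears.
- **That only 66 women would be analysed.** Section 2.9.1 makes 30% of measurements missing, not 30% of women, and the mixed model keeps women with partial data.
- **That surgery type is excluded.** The list is open and the rule could admit it. The cited study found similar mean glucose between procedures, so the article gives no evidence of confounding for that primary measure. It reports no birth-weight difference by procedure. Leaving surgery type out matters little except in the strongest case tested.
- **That weight gain, nutrient deficiencies and hypertension must leave the primary model.** The Background lists nutrient deficiencies beside altered glucose metabolism as possible contributors. Section 2.9.2 seeks an independent association, and the Discussion sets glucose metabolism against weight and caloric intake. Adjusting for these rivals is a defensible choice of estimand. Hypertension is not defined as chronic or gestational, and smoking and time from surgery are not consequences of glycaemia.
- **That four versus five covariates undermines the sample size.** It moves N from 95 to 96.

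**Conclusion.** The concern holds in a limited form. Section 2.9.2 gives two incompatible instructions for the primary model's covariates. The second, read as a screen in the study data, can leave real confounding in place and lets chance decide whether pathway variables are adjusted for. Under the stated assumptions (same direction, 0.2 with both variables, p<0.05 screen) the false-positive rate goes from a nominal 2.5% to about 7% or 10-11%. Under weak or mixed-sign confounding it stays at about 3%. These figures show what the rule can do and do not forecast this study. Naming surgery type is sensible, because it is fixed before pregnancy, known for every woman and reported by the article to differ in glycaemic variability. The evidence does not show that omitting it would distort the result much.

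**What to change.** In section 2.9.2:

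1. Delete the association rule.
2. Prespecify, on subject-matter grounds, a fixed covariate set for the primary model that includes surgery type (bypass or sleeve) together with smoking and time from surgery.
3. State in advance whether the pregnancy-time variables (insufficient gestational weight gain, nutrient deficiencies, and hypertension if gestational) belong to the primary model. Report the slope with and without them as labelled models, so that the total and the adjusted association can both be read.
4. Define hypertension as chronic or gestational.
5. Make the number of covariates agree between sections 2.9.1 and 2.9.2, either by choosing four or by restating the calculation.

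The change is to wording, and the variables are already part of the planned data collection. It costs one or two degrees of freedom: with all five named variables plus surgery type, the plan's own formula asks for 97 women and gives 79.2% power at 95.
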